### Blinding

Although it is impossible to ensure blinding for intervention conductor and the participating women, we will ensure blinding for the outcome measurements and biochemical analyses by independent examiners unaware of group allocation. Participants cannot be blinded for the intervention, but they are asked not to reveal information about their allocation to the examiners. The key of coding concerning group assignment is only known by the programmer of the database that is used during the study.

### Interventions

On the basis of our previous study in postpartum women from Hubei province of China and the latest WHO recommendation [19], we have formed a set of recommendations for women's diet and lifestyle during the postpartum period, which is the guideline for the current intervention study. A comparison between traditional practices for "doing the month" and expected diet and lifestyle that we advocated during the postpartum period are shown in Table 1. It is obvious that our guideline emphasizes the importance of increasing consumption of vegetables and fruits, which is regard as a diet taboo for postpartum women in traditional Chinese practice. In addition, it also emphasizes the importance of maintaining energy balance through reducing excessive energy from meat, eggs and brown sugar and increasing energy expenditure from appropriate physical activity, such as doing maternal keep-fit exercises.

In the past decades, social ecological models have been increasingly used to formulate intervention strategies in comprehensive consideration, because simple interventions are unlikely to work on their own and the development of effective interventions requires strategies that affect multiple settings simultaneously [20]. As shown in Figure 2, a panel of environmental factors that influence the knowledge, belief and practice of postpartum women (the core) has been identified. Microsystem, mainly referred to family members of the individual woman, is crucial immediate environmental factors that should be considered in priority. Exosystem, including surrounding people, such as peers, friends, colleagues, neighbors and care physicians, and sources of knowledge, such as book, magazines, TV show, radio and internet, does not usually directly interact, but that can still affect the individual woman. In addition, we have to consider macrosystem, including history, culture, laws, ethnics, social conditions and economic systems, to give a personalized guide to individual postpartum woman. Previous studies by us and other groups have suggested that main influence factors on the diet and lifestyle of a postpartum woman include the woman's knowledge about postpartum nutrition and health care, the woman or her husband's educational level and family income levels, and the traditional concept learned from her mother in-law (49.4%), mother (34.0%), books and magazines (16.5%), relatives (14.3), friends or colleagues (12.6%) [15,21].

**Figure 2 F2:**
[figure not shown]
**Social Ecological Model showing potential factors that influence postpartum women's belief and practice**.

Therefore, we have formulated a three-dimension comprehensive intervention strategy (Table 3), which incorporates intervention measures simultaneously to individual postpartum woman, their family members and community environment to maximize the effectiveness of our multicenter trial. For individual postpartum woman, we will set antepartum participatory training courses, provide specially prepared brochures and supporting VCD, set up a specialized counseling hotline and give individual bedside guidance after birth. For their family members, we will invite every postpartum woman's husband and mother to take part in workshops or seminars, making them know some basic knowledge of postpartum care, and persuading them to promote adoption of the diet and lifestyle we advocated by the postpartum woman. For community environment, we will put up posters about basic knowledge of postpartum care in the community bulletin boards for general population educating and mobilize community leaders and heads from and maternal and child health centers for maximum support.

**Table 3 T3:** Summary of our three-dimension comprehensive intervention strategy

Dimensions	Subjects	Strategies and Measures
1	Postpartum woman	- Participatory training for woman who expects to childbirth with 1 month - Providing specially prepared release of "Chinese women's postpartum reasonable diet and lifestyle program" (Universal Edition) and supporting VCD, to facilitate self-learning at home - Setting up a specialized counseling hotline to answer the questions from postpartum woman and their family members - Individual bedside guidance for postpartum woman, focusing on how to correctly adjust her diet and life style during postpartum period

2	Family members	Inviting every postpartum woman's husband and mother to take part in workshops or seminars, making them know some basic knowledge of postpartum care, and persuading them to promote adoption of the diet and lifestyle we advocated by the postpartum woman

3	Community support	- General population educating via putting up posters about basic knowledge of postpartum care in the community bulletin boards - Mobilizing community leaders and heads from and maternal and child health centers for maximum support

### Outcome measurements

Major measurements before and after the intervention trial are shown in Table 4. The primary outcome for the current study is the changes in the knowledge and belief about postpartum practice among the women, which expect the women in intervention group know more about the nutritional requirements in postpartum period and the potential benefit from a balanced diet with appropriate amount of animal food and abundant amount of plant-derived food. The secondary outcome for the current study is the changes in the nutritional status, including both macronutrients and micronutrients level, which reflects the real action of adopting our recommendation in their everyday food intake. The tertiary and the most important outcome is the changes in postpartum recovery and health status, including a promotion for uterine involution and a reduction of postpartum diseases such as puerperal infection, fever, constipation, hemorrhoids, anal fissure, breast disease, oral ulcers, gum bleeding, anemia, pains (headache, heel pain, back pain, leg pain, joint pain, leg cramps, etc.) and postpartum depression.

**Table 4 T4:** Overview of the Measurements before and after the Intervention

Indexes	Assessing methods
Nutrition and health knowledge	Questionnaires

Puerperium diet and lifestyle	
Diet patterns	24-hour dietary recording and FFQ
Health-related behaviors	Questionnaires
Physical activities	Questionnaires

Assessment of nutritional status	
Macronutrients intake (protein, lipid and carbohydrate, and dietary fiber from cereals, sugar, vegetables, fruits, meat, eggs, milk, soybeans, etc.)	24-hour dietary recording and FFQ, which include both food categories and amount
Micronutrients intake	
Vitamins	HPLC for vitamin A and vitamin D, load test for B vitamins and vitamin C
Minierals	AAS for serum calcium, iron and zinc
Nutrient Metabolism	
Blood glucose and lipid profiles, including total cholesterol, HDL-C, LDL-C, triglycerides	Automatic biochemical analyzer

Postpartum recovery and health status	
Anthropometric measurements, including height, body weight, and BMI	BMI = body weight (kg)/height (m^2^)
Body recovery, including duration for lochia, amount and duration of postpartum hemorrhage, degree of uterine involution	Diagnosis by specialized obstetricians
Diseases prevalence, including puerperal infection, fever, constipation, hemorrhoids, anal fissure, breast disease, oral ulcers, gum bleeding, anemia, pains (headache, heel pain, back pain, leg pain, joint pain, leg cramps, etc.)	Diagnosis by specialized doctors
Postpartum depression	Assessed by the Edinburgh Postnatal Depression Scale

Milk secretion and neo development	Assessed by specialized doctors

FFQ indicates food frequency questionnaires; HPLC, high performance liquid chromatography; AAS, atomic absorption spectrophotometry; HDL-C, high density lipoprotein cholesterol; LDL-C, low-density lipoprotein cholesterol; BMI, body mass index

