**Discussion:**

To our knowledge, this current study is the first and largest multicenter RCT which focus on the effectiveness of diet and lifestyle intervention on reducing the incidence rate of postpartum diseases and improving health status in postpartum women. We hypothesize that the intervention will reduce the incidence rates of postpartum diseases and improve nutrition and health status due to a balanced diet and reasonable lifestyle in comparison with the control condition. If so, the results of our study will provide especially important evidence for changes in both the concept and action of traditional postpartum practice in China.

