## Methods/Design

### Objectives

This multicenter RCT is designed to assess the effectiveness of a diet and lifestyle intervention in postpartum women in China, including a short-term effect on reducing health problems during puerperium period and a long-term effect on improving health status in women and their offspring over a two-year period.

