### Sample size

Sample size has been calculated as the following formula [18]:

, in which *p*_*1 *_indicates incidence rate in control group, *p*_*2 *_indicates incidence rate in intervention group and  indicates average of *p*_*1 *_and *p*_*2*_. Z_α/2 _is 1.96 when significance level (α) is 0.05 and Z_β _is 1.64 for power (1 - β) is 0.90.

Take constipation, a typical diet-related digestive disorder, for example. The incidence rate of constipation in our previous study is 20.95% in the control group [16]. We aim to reduce the incidence rate by 50%, which is 10.475%, the sample size N = = 309.89 ≈ 310 for each group. On the basis of the above calculation, a sample size of 800 participants (400 in the intervention group and 400 in the control group) has been determined, considering a certain attrition rate. This sample size is adequate, with statistical power >80%, for nearly all the major outcomes, including changes in nutritional status and health status.

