## Discussion

It is generally accepted that a balanced diet comprising abundant intake of whole cereals, fruits, vegetables and a suitable amount of fish, meat, eggs and milk is essential for maintaining our health. However, postpartum women in China are traditionally advised to follow a special dietary and lifestyle pattern, which is quite different from the dietary and lifestyle patterns they maintain before and after postpartum period [15]. Several studies have paid attention to explore the relationship of postpartum practice and consequent health problems in Chinese women [23,24]; however, as we know, it is hard to draw a clear causation in cross-sectional studies.

To our knowledge, this study is the first and largest multicenter RCT which focus on the effectiveness of diet and lifestyle intervention on reducing the incidence rate of postpartum diseases and improving health status in postpartum women. This evidence-based study is designed on the basis of data from our previous study in three regions in Hubei province of China [15,16], incorporating with the latest WHO recommendations [19]. The major limitation of this study is that the participants that we will recruit are mainly Chinese Han women, whereas the postpartum practices vary among different national minorities in China. Further research on different minority populations will be very interesting.

We hypothesize that the intervention will reduce the incidence rates of postpartum diseases and improve nutrition and health status due to a balanced diet and reasonable lifestyle in comparison with the control condition. If so, the results of our study will provide especially important evidence for changes in postpartum diet and lifestyle. The fantastic reform in both the concept and action of traditional postpartum practice in China will be expected.

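### The declared primary outcome is knowledge and belief, but the objective, the hypothesis and the only sample size calculation concern other outcomes, chiefly health

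*Protocol article*

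**What the plan says.** The Outcome measurements section ranks three outcomes:

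- First: "The primary outcome for the current study is the changes in the knowledge and belief about postpartum practice among the women".
- Second: "The secondary outcome for the current study is the changes in the nutritional status, including both macronutrients and micronutrients level".
- Third: "The tertiary and the most important outcome is the changes in postpartum recovery and health status". Constipation is listed here, among many other postpartum conditions.

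Other sections describe what the trial is for:

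- Objectives: "a short-term effect on reducing health problems during puerperium period and a long-term effect on improving health status in women and their offspring".
- Discussion: "We hypothesize that the intervention will reduce the incidence rates of postpartum diseases and improve nutrition and health status due to a balanced diet". The Abstract states the same hypothesis.
- Sample size: "Take constipation, a typical diet-related digestive disorder, for example". The section then takes 20.95% in the control group, aims to halve it to 10.475%, and obtains 309.89, rounded to 310 per group. This is raised to 400 per group for attrition at an unstated rate. Power above 80% is also asserted for nearly all major outcomes, with nutritional and health status as the examples and no inputs shown.

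Table 4 measures knowledge by questionnaire. Table 3 lists training, printed and video material, a hotline and bedside guidance as the measures aimed at the woman herself.

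**The concern.** A primary outcome should be the measure on which the main question is answered and for which the trial is sized. Here the label falls on a different outcome. Neither the objective nor the hypothesis mentions knowledge or belief, and the sample size section gives no input for them. The outcome the authors themselves call most important is ranked third.

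The choice also matters because of what the intervention does. It teaches postpartum nutrition and care, and the declared primary outcome asks whether women know and believe more about postpartum nutrition and care. That is the step on which the intervention acts most directly. A gain there is compatible with no change in diet and no illness prevented. If the report follows the labels, the headline result would not answer whether the programme improves health. If the report instead promotes a health outcome after the data are in, readers could not exclude that it was chosen for its result.

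**Working it through.** **1. Which outcome each part of the article addresses**

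| Part of the article | Knowledge and belief | Nutritional status | Recovery and health |
|---|---|---|---|
| Objectives | no | no | yes |
| Hypothesis (Abstract; Discussion) | no | yes | yes |
| Sample size calculation | no | no | yes (constipation) |
| Unsupported claim of power above 80% (Sample size) | not named | named | named |
| Rank (Outcome measurements) | primary | secondary | tertiary, but most important |

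Only the rank favours knowledge and belief.

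**2. The plan's own sample size**

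Inputs (Sample size section): p1 = 0.2095, p2 = 0.10475, difference d = 0.10475, z values 1.96 and 1.64. Mean rate p̄ = (0.2095 + 0.10475)/2 = 0.157125.

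n = [1.96·√(2p̄(1−p̄)) + 1.64·√(p1(1−p1) + p2(1−p2))]² / d²

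- First term: 1.96 × √0.26487 = 1.0087
- Second term: 1.64 × √0.25939 = 0.8353
- n = (1.8440)² / 0.010973 = 309.89

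The stated 310 per group is reproduced, so the trial was sized on an illness outcome that the article ranks third. As a separate matter, 1.64 is the z value for 95% power, not the labelled 90%; z = 1.2816 would give 252 per group.

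**3. Power for constipation if it were primary**

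Power = Φ{[d√n − 1.0087] / √0.25939}, with √0.25939 = 0.5093.

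- n = 310: (1.8443 − 1.0087)/0.5093 = 1.641, power about 95.0%
- n = 400: (2.0950 − 1.0087)/0.5093 = 2.133, power about 98.4%

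**4. Power for knowledge and belief**

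The article gives no difference or SD, so a required size cannot be computed. Assume a roughly normal score and a standardised difference δ: power ≈ Φ(δ√(n/2) − 1.96), with √(310/2) = 12.45 and √(400/2) = 14.14.

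| Assumed δ | Power, 310 per arm | Power, 400 per arm |
|---|---|---|
| 0.1 SD | Φ(−0.715) ≈ 24% | Φ(−0.546) ≈ 29% |
| 0.2 SD | Φ(0.530) ≈ 70% | Φ(0.868) ≈ 81% |
| 0.3 SD | Φ(1.775) ≈ 96% | Φ(2.283) ≈ 99% |

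The answer depends almost wholly on the assumed effect.

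**The case against.** The strongest reply is that the three ranks describe a causal chain: women learn, then eat differently, then recover better. The Outcome measurements section runs in that order and describes nutritional status as showing whether the advice was acted on. The Interventions section lists the woman's knowledge among the main influences on diet and lifestyle. This reading is plausible and would make the problem closer to mislabelling than to testing the wrong question. But the article does not state it, and the label used is primary outcome. The order of a mechanism is not an order of inference, so the wording needs correcting on either reading.

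Three further points stand as limits:

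- The hypothesis includes nutrition as well as disease and health, so not everything outside the label points to health alone.
- Constipation is introduced only as an example. It is the only outcome with a calculation, not one the authors singled out as their main endpoint.
- Belief is more than recall of course content. The Background reports that belief in the practice persists regardless of education, acculturation and time since immigration.

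Two stronger readings are tempting. A reader might infer that a positive primary result is practically assured. The document does not support this: it gives no effect size, the power range above is wide, and community posters could reach control women and narrow the difference. A reader might also infer that the sized outcome has been left without any confirmatory role. The article sets no testing hierarchy, no division of alpha and no rule tying effectiveness to the primary outcome. Statistical methods plans the same mixed models for the major outcomes generally, and the Discussion ties its conclusion to the health and nutrition hypothesis.

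**Conclusion.** The point holds as an internal contradiction that must be reconciled. The outcome labelled primary is not the one named in the objective or hypothesis, has no sizing inputs, and could improve with no health benefit because it measures what is taught. The outcome called most important, which contains the only sized endpoint, is ranked third.

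The contradiction itself rests on the text and needs no assumption. The 95% and 98% power for constipation assume the article's rates (20.95% and 10.475%), two-sided 5% significance, and 310 or 400 women analysed per group. The figures for knowledge assume a roughly normal score and effects that the article does not give. They show only that success on knowledge cannot be predicted from the document.

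**What to change.** In Outcome measurements, before outcome data are seen:

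- Name one defined health outcome as primary. Incidence of constipation during the puerperium is the natural choice because it alone has a calculation, and the planned size supports it. Another single health outcome would also resolve the contradiction if it were sized.
- Make nutritional status and the remaining recovery and illness outcomes secondary.
- Describe knowledge and belief as an intermediate (process) outcome.
- State that effectiveness will be claimed on the primary health outcome.
- Check the registration, which was not reviewed here, and amend it if it carries the same ranking.

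The alternative is to keep knowledge and belief as primary. That would mean rewriting the objective, hypothesis and sample size around them, and would abandon the question the trial says it asks.

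The cost is modest: no additional women and no new measurements, since Table 4 already includes constipation. Knowledge loses its primary status. The chosen outcome also needs a clear case definition and time window, with one consistent measure: Table 4 speaks of disease prevalence, whereas the sample size uses incidence.

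### The primary outcome is knowledge and belief, but the outcome called most important, the objective, the hypothesis and the only sample-size calculation all concern health, so the hierarchy needs realigning

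*Protocol article*

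**What the plan says.** The Outcome measurements section of the protocol article sets three tiers:

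- Primary: "The primary outcome for the current study is the changes in the knowledge and belief about postpartum practice among the women".
- Secondary: "The secondary outcome for the current study is the changes in the nutritional status".
- Third: "The tertiary and the most important outcome is the changes in postpartum recovery and health status". This tier covers uterine involution, a list of postpartum diseases and pains that includes constipation, and depression.

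The Objectives section gives the aim as "a short-term effect on reducing health problems during puerperium period", together with longer-term health of women and offspring over two years. The Discussion part of the Abstract states the hypothesis: "We hypothesize that the intervention will reduce the incidence rates of postpartum diseases and improve nutrition and health status". The article's own Discussion repeats it.

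The Sample size section introduces its calculation with "Take constipation, a typical diet-related digestive disorder, for example". It arrives at 310 per group, raised to 400 per group for attrition. It then claims more than 80% power for nearly all major outcomes and names nutritional and health status among them. Knowledge and belief are not named.

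**The concern.** The primary outcome is normally the one on which a trial is declared positive or not, and the one for which it is sized. Here those roles are split. The primary label sits on knowledge and belief, while the declared importance, the objective, the hypothesis and the sample-size inputs sit elsewhere.

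The content of the primary outcome makes this more than a labelling matter. The Interventions section and Table 3 give the intervention arm training courses, printed material, a VCD, a hotline and bedside guidance. Table 4 measures nutrition and health knowledge by questionnaire. The Blinding section accepts that participants cannot be blinded, and blinded examiners give little protection to answers that come from the women themselves.

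A better score among women who were taught the material is therefore to be expected if the programme is delivered. It would satisfy the primary outcome even if no disease rate moved. The question the trial was set up to answer would then rest on a third-tier group of outcomes from which this document selects no main test.

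**Working it through.** **1. Statements side by side (protocol article)**

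| Section | What it points to | Knowledge or belief mentioned? |
|---|---|---|
| Objectives | Fewer puerperal health problems; longer-term health | No |
| Hypothesis (Abstract and Discussion) | Disease incidence; nutrition and health status | No |
| Sample size, calculation | Constipation | No |
| Sample size, general power claim | Major outcomes, naming nutritional and health status | Not named |
| Outcome measurements, primary | Knowledge and belief | Yes |
| Outcome measurements, most important | Recovery and health (third tier) | No |

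Only the primary label points to knowledge and belief.

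**2. Reproducing the stated sample size**

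Inputs from the Sample size section:
- p1 = 0.2095 and p2 = 0.10475 (a 50% reduction), so the average p̄ = 0.157125.
- The critical value "is 1.96 when significance level (α) is 0.05".
- The second multiplier "is 1.64 for power (1 - β) is 0.90".

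The pooled two-proportion formula fits the article's definitions:

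n = [1.96·√(2p̄(1−p̄)) + Zβ·√(p1(1−p1) + p2(1−p2))]² / (p1−p2)²

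- √(2 × 0.157125 × 0.842875) = 0.51466, and × 1.96 = 1.00873
- √(0.16561 + 0.09378) = 0.50930, and × 1.64 = 0.83525
- n = (1.84399)² / (0.10475)² = 309.89

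This matches the article exactly. Every input is a constipation rate or a normal quantile. Nothing in the calculation refers to knowledge or belief.

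A separate matter: 1.64 is the multiplier for about 95% power, not 90%. At 90% the same method gives 252 per group, so the slip errs on the large side and does not affect this point.

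**3. Power if constipation were primary**

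Power = Φ{[(p1−p2)√n − 1.00873] / 0.50930}

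- n = 310: (1.84431 − 1.00873) / 0.50930 = 1.641, power 95.0%
- n = 400: (2.09500 − 1.00873) / 0.50930 = 2.133, power 98.4%

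The second figure assumes no attrition. Going from 400 to 310 corresponds to a loss of 1 − 310/400 = 22.5%. The article gives no attrition figure of its own.

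**4. Power for another health endpoint**

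The control rates below are assumptions, not figures from the article. Each is taken to be halved by the intervention.

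| Assumed control rate | Power, 310 per group | Power, 400 per group |
|---|---|---|
| 15% | 84% | 92% |
| 10% | 66% | 77% |
| 5% | 37% | 46% |

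A rarer condition is therefore not automatically covered by the present size.

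**5. If knowledge and belief stayed primary**

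The article gives no scale, standard deviation or target difference, so no required size can be computed. In standard-deviation units the detectable difference is (1.96 + Zβ)·√(2/n). At 400 per group this is 0.20 SD for 80% power and 0.23 SD for 90%. At 310 per group it is 0.23 and 0.26 SD.

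**The case against.** The best defence is that the three tiers follow a causal chain: knowledge and belief change first, diet follows, health comes last. The Outcome measurements section supports this by treating nutritional status as the sign that advice was acted on. The Interventions section names the woman's knowledge among the main influences on her diet. For an educational programme a proximal primary outcome can be a deliberate choice. This explains the order of the tiers. It does not explain why the last tier is called most important, or why the objective, hypothesis and sample size pass over the first.

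Several parts of the other side's case do stand, and they limit what may be concluded:

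- Constipation is offered as an example. A reader might infer that it is the trial's hidden primary endpoint, but the text does not designate it as such.
- The hypothesis also covers nutrition and health status, and the third tier also covers recovery. The conflict is therefore not purely between knowledge and disease.
- A reader might infer that the long list of health outcomes will be tested item by item with no control of false positives. The article does not say so. It names families of tests and mixed models, and multiplicity rules may sit in an analysis plan that is not shown.
- A reader might infer that a positive primary result would show nothing beyond delivery of the teaching. The outcome includes belief as well as recall, in a setting where the article describes strong family influence, so a change could mean more than that. It would still not be a health effect.

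**Conclusion.** The point holds as a misalignment fixed in the protocol text. The primary label falls on an outcome that the objective, the hypothesis and the sample-size calculation do not use. The outcome declared most important is ranked third, with no component singled out. An analysis plan could specify tests within that tier, but it could not make one of them primary without contradicting the protocol.

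The consequence is interpretive: the trial can succeed on its primary outcome with no change in health. The conclusion rests on the wording of the article and on the questionnaire being answered by unblinded women. It does not rest on any claim about false-positive rates. Nor does it show that the trial is too small for its primary outcome, since the inputs needed to judge that are not given. For constipation the planned size is ample: 95.0% power at 310 per group and 98.4% at 400 with no losses, if the 20.95% control rate and the halving are realistic.

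**What to change.** Before outcome data are seen, name one pre-specified health endpoint as primary.

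- **Endpoint.** Incidence of constipation during the puerperium is the option the trial is already sized for. Table 4 assigns its diagnosis to doctors, which brings it under the blinded-examiner arrangement. Another health endpoint is equally legitimate but needs its own control rate, target difference and power check.
- **Other outcomes.** Reclassify knowledge and belief as a process (uptake) outcome. Keep nutritional status and the remaining health outcomes as secondary or exploratory, and say which.
- **Text.** Align the Objectives, Outcome measurements and Sample size sections, and update the registry entry to match.

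If the sponsor prefers to keep knowledge and belief as primary, the objective, hypothesis and sample size would have to be rewritten around it, with a stated scale and target difference.

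The cost is protocol wording and a registry update, with no extra participants or data. There are two downsides: knowledge loses its headline place, and a single condition as primary does not by itself answer for all postpartum disease or recovery. The article does not give the trial's status. If outcome data have already been seen, the change must be reported as made afterwards.
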